### Blinding

Blinding of group allocation is not possible in the emergency department for the study participants, parents/carers or research staff as ethics preclude the administration of placebo intravenous fluid boluses. Data will be blinded to the data analysist by labelling the groups with non-identifying terms until data collection has been completed. Breakage of blinding will be possible for the Data Safety and Monitoring Board (DSMB) in the interim. A list of the randomisation code will be kept by the independent statistician in Malawi who can communicate with the data manager and the DSMB when needed. A sealed envelope containing the randomisation code will be kept in the investigator site file.

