### Randomisation and group allocation

Randomisation will be to the two arms of the trial: the intervention arm and the control arm. Children with severe malnutrition will be randomised separately in another stratum to ensure the same number of children in each arm of each stratum. An independent statistician who is not part of the research team has produced a computer-generated randomisation list using a two-stage process to ensure allocation concealment. The computer first randomly selects whether the block will contain six or eight patients and then randomly chooses one of the possible different allocation blocks for the selected size.

The investigators assign the subject identification numbers sequentially and group allocation is determined when the research staff opens an opaque envelope prepared in advance by the independent trial statistician. Envelopes are opened in the emergency department as soon as a child has been identified as eligible for the trial. The study identification number will be retained throughout the study and will appear on all case report form pages and source documents.

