### Data collection and management

Electronic clinical record forms (CRFs) have been developed from the paper drafts with the assistance of Malawi College of Medicine Research Support Centre’s Data Management team using Open Data Kit (https://opendatakit.org). Data are collected on Android tablets and uploaded to a database on the day of collection. The data management team provides the investigators with weekly data reports including numbers enrolled and any problems in data collection including serious adverse events (SAEs) and protocol violations. Details about the data management plan are in the Data Management Standard Operating Procedures, which can be requested from the study team. Data access will be granted to investigators and the assigned study statisticians with whom a Mutual Confidential Disclosure Agreement has been signed (available upon request from corresponding author). Data will be exported for analysis to a statistics software package such as STATA v 12 for analysis. Principal analysis will be on an intention-to-treat principle and all statistical analysis will be done by a statistician who is independent from the study research team.

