### Trial monitoring and safety

Trial monitoring will be done by an independent clinical trial monitoring team at pre-decided scheduled visits: before study-start; after the enrolment of 20 patients; at 50% enrolment; and at the end of the study. A three-member sponsor-independent DSMB who are not involved in the design or conduct of the study has been appointed to deal with any safety issues that arise while the trial is in progress and to scrutinise the interim analysis. The DSMB consists of one epidemiologist, one professor in paediatrics and one professor in biostatistics. SAEs are identified by the study team and reported to an independent Clinical Monitor within 48 h. Following the Clinical Monitor’s assessment, the SAEs are sent to the DSMB and to the College of Medicine Research and Ethics Committee. Interim analyses will be conducted by the trial statistician and reviewed by the DSMB. The intention is for an analysis conducted at 50% of information time (percentage of participants with data for the primary endpoint) though the DSMB committee may suggest other or additional times for interim analyses. The interim analysis will be done for trial safety including review of eligibility and treatment, summary of response, survival and any adverse events (AEs). Stopping rules are detailed in the Statistical Analysis Plan, which can be requested from the study team. Any important protocol modifications will be communicated to the IRB, the DSMB and the trial registry.

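### The analyst's masking ends before the final analysis, and the article does not say that the final analyst is someone other than the statistician who knows the allocations

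*Protocol article*

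**What the plan says.** The Blinding section explains that participants, carers and research staff in the emergency department cannot be blinded. It then gives one masking measure, with its end-point: "Data will be blinded to the data analysist by labelling the groups with non-identifying terms until data collection has been completed". The same section lets the DSMB break the blind at the interim and says where the code is held: "A list of the randomisation code will be kept by the independent statistician in Malawi".

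Four other statements describe what statisticians do:

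- Randomisation and group allocation, on the list: "An independent statistician who is not part of the research team has produced a computer-generated randomisation list".
- The same section, on the envelopes: a member of the research staff "opens an opaque envelope prepared in advance by the independent trial statistician".
- Trial monitoring and safety: "Interim analyses will be conducted by the trial statistician and reviewed by the DSMB".
- Data collection and management: "all statistical analysis will be done by a statistician who is independent from the study research team". This section also grants data access to study statisticians, in the plural.

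The Analysis plan specifies intention-to-treat logistic regression for in-hospital and 24-hour mortality, with sub-group analyses for both, and refers to a separate Statistical Analysis Plan for details. The section on a priori sub-groups lists 11 sub-groups, announces per-protocol analyses, and lists protocol violations separately for each arm.

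**The concern.** Masking an analyst matters most when results by arm are being produced and decisions about the data can still be made. Final cleaning, who belongs in the per-protocol set, any modelling detail still open and the run of the analyses themselves all follow the last data entry. A rule that releases the labels at that moment removes the protection just before it is needed. Since no other masking is claimed, the final analysis would be run with the arms known.

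The second difficulty is who is masked. Someone who prepared the envelopes cannot be masked by relabelling the groups. If the person who knows the allocations also analyses outcomes, the labels have no effect for that person. The article should therefore make clear that the masked analyst is a different person, and it does not.

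**Working it through.** No figure in the plan bears on this point. The stated sample size of 1266 reproduces exactly (633 per arm, two-sided test with continuity correction), and no change to the masking rule would alter it. The check is therefore a comparison of sections.

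**Step 1: when masking ends.** The order of events is data collection, then final cleaning and lock, then final analysis. The Blinding section puts the release of labels at the end of the first stage. The sections on data management, the analysis plan and trial monitoring were read for anything that moves it later. None does.

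**Step 2: who does what.**

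| Task | Role as named | Section |
|---|---|---|
| Produces the list | independent statistician, outside the research team | Randomisation and group allocation |
| Prepares the envelopes | independent trial statistician | Randomisation and group allocation |
| Keeps the code | independent statistician in Malawi | Blinding |
| Runs interim analyses | trial statistician | Trial monitoring and safety |
| Runs all statistical analysis | statistician independent of the research team | Data collection and management |
| Is masked | data analyst | Blinding |

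Rows two and four share a title, and one of those tasks gives knowledge of allocation. Rows one and five carry nearly the same description. Row five covers all analysis, so on its face it includes both the interim work in row four and the work of the masked analyst in row six. The roles may be filled by several people, but the article never says which coincide.

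**Step 3: what is open to judgement after data collection.**

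- Primary and secondary analyses: the outcomes are deaths, the population is everyone randomised and the model type is named. Little is left to choose.
- Sub-groups: 11 sub-groups × 2 outcomes = 22 results. That counts how much is analysed and does not measure bias. The groups are defined in advance, and most rest on recorded facts such as temperature, age, glucose, blood slide and blood culture. Severe malnutrition is the randomisation stratum, so it is classified before allocation.
- Per-protocol set: there is more room here. The list of violations is introduced as inclusive rather than complete, and no tolerance is given for a dose to count as incorrect. Extra glucose testing of a control child in the emergency department is a violation, while The intervention section allows re-checking when clinically warranted. These passages must be reconciled before such children can be classified consistently.

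**Step 4: can later masking cover the per-protocol set?** No. A missed bolus can be a violation only in the intervention arm, and dextrose given in the emergency department only in the control arm. Whoever applies the criteria knows the arm. What can be withheld is the child's outcome.

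**The case against.** The strongest defence is that the article condenses a fuller set of documents. The Statistical Analysis Plan and the data management procedures exist, are not shown, and are the usual place for database lock, code release and statistician assignments. That stands for anything the article leaves out. It does not answer the end-point of masking, which the article states; a different rule in the analysis plan would contradict the published one. Even if completion of data collection is read generously to include lock, the final analysis still follows it.

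Three stronger readings are tempting, and the article supports none of them.

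- A reader might infer that the masking is worthless. Labels masked during recruitment still limit knowledge of results by arm while an open-label trial runs.
- A reader might infer that one person holds the code and performs the final analysis. That rests on role titles alone. The Blinding section names the analyst and the code holder separately, and more than one statistician has data access. An independent statistician who holds the code and serves the DSMB is a usual arrangement.
- A reader might infer that investigators receive a running safety comparison by arm, because the data managers send them "weekly data reports including numbers enrolled and any problems in data collection including serious adverse events (SAEs) and protocol violations". The article does not say that serious adverse events are tabulated by arm. The study team is unblinded and identifies those events itself.

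It is also fair to object that violations go into the weekly reports, so many are logged during the trial rather than first judged at its end. That narrows the per-protocol concern, but the criteria themselves remain open.

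**Conclusion.** The point holds in a limited form. As published, the trial's only masking ends before the final analysis, and the article does not separate the person who knows the allocations from the person who analyses the outcomes. The first part is a stated rule. The second is an unresolved ambiguity, not evidence that one person does both.

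The expected effect on the intention-to-treat mortality result is small, given an objective outcome and a named model. It cannot be quantified from the article, which gives no violation rate and no account of choices left open. The room for influence is larger in the per-protocol analysis, which is supplementary. The sub-groups add volume more than discretion. This conclusion assumes that the published wording is the operative rule and that the analysis plan does not replace it.

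**What to change.** - **Blinding section, end-point.** State that group labels stay masked until the database is locked and the intention-to-treat analyses of in-hospital and 24-hour mortality, together with the a priori sub-group analyses, have been run on the masked labels.
- **Roles.** Say which statistician produced the list and envelopes, which holds the code, which runs the interim analyses for the DSMB and which runs the final analysis. State that the code holder does not run the final analysis.
- **Data for the masked run.** Leave out fields that reveal the arm, in particular total dextrose received and the arm-specific violation items. With them present, the labels could be decoded.
- **Per-protocol set.** Do not present this classification as blind to arm. Complete the criteria in writing, reconcile the two passages on re-testing control children, and sign off membership before lock by people who do not see outcomes.

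The cost is a few sentences in the protocol and analysis plan and an allocation of tasks among statisticians already involved. Sample size, treatment and data collected are unchanged. At manuscript submission 60 of 1266 children had been randomised, so the final analysis was still far off.

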### Trial monitoring and safety

Trial monitoring will be done by an independent clinical trial monitoring team at pre-decided scheduled visits: before study-start; after the enrolment of 20 patients; at 50% enrolment; and at the end of the study. A three-member sponsor-independent DSMB who are not involved in the design or conduct of the study has been appointed to deal with any safety issues that arise while the trial is in progress and to scrutinise the interim analysis. The DSMB consists of one epidemiologist, one professor in paediatrics and one professor in biostatistics. SAEs are identified by the study team and reported to an independent Clinical Monitor within 48 h. Following the Clinical Monitor’s assessment, the SAEs are sent to the DSMB and to the College of Medicine Research and Ethics Committee. Interim analyses will be conducted by the trial statistician and reviewed by the DSMB. The intention is for an analysis conducted at 50% of information time (percentage of participants with data for the primary endpoint) though the DSMB committee may suggest other or additional times for interim analyses. The interim analysis will be done for trial safety including review of eligibility and treatment, summary of response, survival and any adverse events (AEs). Stopping rules are detailed in the Statistical Analysis Plan, which can be requested from the study team. Any important protocol modifications will be communicated to the IRB, the DSMB and the trial registry.

## Discussion

The risk of AEs due to dextrose administration is low and is mainly related to complications of cannulation such as infections or subcutaneous fluid administration. The skin will be disinfected before pricking and the cannula removed in case of signs of subcutaneous fluid administration. Dextrose is a sugar that is rapidly metabolised to carbon dioxide and water in the body, providing energy. The administration of 10% dextrose may cause irritation to blood vessels with an associated discomfort that is self-limiting. Any SAEs occurring in participants, whether likely to be due to the trial or not, will be systematically recorded and reported.

The use of intraosseous needles will be applied in situations of difficult intravenous cannulation. Considering that all study children present with one or many WHO Emergency sign(s), it is considered clinically warranted to ensure a soon access to the systemic venous system, but will only be applied after repeated attempts of intravenous cannulation. In cases of intraosseous cannulation, standard procedures will be applied to avoid complications such as proper cleaning and removal of the needle not later than 24 h after insertion.

Knowledge about the impact of a raised blood glucose cut-off level for dextrose administration in acutely ill children will inform local, national and global management guidelines, potentially improving survival rates.

Study findings will be communicated with the hospital management, the College of Medicine and the Malawian Ministry of Health as soon as available. Results will be further disseminated through scientific publications, presentations at international child health scientific conferences and to the WHO. Trial presentations will adhere to the CONSORT statement [20]. If the findings have public interest, they will be disseminated through newspapers and radio broadcasting

### Trial status

Enrolling since 5 December 2016. At the time of manuscript submission on 5 April 2017, 60 patients (4.8% of the final sample size) had been randomised.

## Abbreviations

COMREC: College of Medicine Research and Ethical Committee
CRF: Clinical record forms
DSMB: Data Safety and Monitoring Board
ETAT: Emergency Triage Assessment and Treatment
IRB: Institutional review board
ODK: Open data kit
SAE: Serious adverse events
SPIRIT: Standard Protocol Items, Recommendations for Interventional Trials
WHO: World Health Organization
